Study staff provided telephone follow-up on recruitment mailings and contacts by placing up to six calls at various days and times. The study was explained and interested survivors were screened for eligibility. Inclusion and exclusion criteria were established to target survivors who were most in need and who could best benefit from a web-based diet and exercise intervention. Inclusion criteria were as follows: (1) BMI > 25 kg/m^2^ [10]; (2) vegetable and fruit intake <2.5 cups/day; (3) moderate-to-vigorous physical activity (MVPA) <150 min/week [11]; (4) completion of primary cancer treatment; (5) English speaking and writing; (6) educational attainment of 5th grade or higher; and (7) daily use of the Internet and mobile phone access. Exclusion criteria were few and limited to those who were already adhering to modified diets or enrolled in an exercise program, residing in assisted or skilled nursing facilities, or recently advised by their physician to limit physical activity and/or having health issues that might make participation in an unsupervised weight loss intervention unsafe (e.g., pregnancy, severe orthopedic conditions, end-stage renal disease, metastatic cancer or other cancers with poorer survival, paralysis, dementia, blindness, unstable angina, untreated stage 3 hypertension, recent history of heart attack, congestive heart failure or pulmonary conditions that required oxygen or hospitalization within 6 months) [12]. Once initial eligibility was established and cancer case status was verified by treating physicians of any self-referrals, the survivor was asked to identify a local support partner (preferably within a 10-min drive) and have them contact the research team for screening. Supportive partners were required to meet all inclusion/exclusion criteria, except for being a cancer survivor.

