### 2.6. Statistical Power

This 2-arm RCT formally tests for differences in the loss of body weight from baseline to 6-months that occurs among 56 dyads (with each dyad comprised of a survivor and a partner) who are randomized to two study arms. All other analyses and tests are exploratory. Power calculations are based on the following assumptions: (1) the retention rate will be identical to the DAMES trial (i.e., 90%), which is conservative as the duration for DUET is only 6 months instead of 12 months; (2) the eHealth intervention will promote weight losses of ~3.46 kg during the 6-month study period (similar to those observed in the Healthy Moves tailored-print, web-based, spousal support intervention—see companion article by Carmack et al. in this Nutrients edition [39]), whereas the control arm will be weight stable—a conservative estimate, since the average American gains 0.5–1 kg/year [40]); and (3) two-sided tests at an alpha level of 0.05 will be used. Given these assumptions, along with those of a two-sided two-group *t*-test, a standard deviation of 4.6 kg (from Healthy Moves [39]), and a sample size of 25 dyads per arm (allowing for 90% retention of the initial 28 dyads per arm), there is at least 80% power to detect differences in weight loss of −3.72 kg or greater between the two arms.

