### 2.7. Data Analyses

The primary analysis will be performed on an intent-to-treat basis using baseline to 6-month data. Arm differences in weight loss will be assessed using a mixed linear model which accounts for the covariance between the dyad members. Specifically, mixed models repeated measures analyses will be used to test differences between arms, the two time points, and the potential interaction between arm and time point simultaneously. An appropriate structure for the covariance matrix (e.g., unstructured) will be selected using the final data. Clinical and demographic covariates of interest will be included in these models. The Tukey-Kramer multiple comparisons test will be used to determine which pairs of means are significantly different. Overall cross-sectional comparisons of continuous variable at baseline will be performed using the two-group *t*-test to determine if there are any differences remaining between the arms after randomization. For categorical variables, comparisons between arms will be performed using the two-group chi-square test (or Fisher’s exact test if the assumptions for the chi-square test are not tenable). The strength of the relationship between pairs of variables will be examined using Pearson (or Spearman, if needed) correlation analyses. Distributions of continuous study variables will be examined using stem-and-leaf, box, and normal probability plots and the Kolmogorov-Smirnov test; any of these variables that deviate from a normal distribution will be transformed prior to analysis or will be analyzed using non-parametric methods such as the Wilcoxon rank-sum test.

Statistical tests will use an alpha level of 0.05 and will be two-sided. SAS software (version 9.4 or later; SAS Institute, Inc., Cary, NC, USA) will be used to perform all statistical analyses. Analyses of secondary outcomes will occur similarly, though analyses are exploratory, and as such will not be controlled for multiple testing. To identify predictor variables associated with program efficacy, e.g., social support (type, amount), self-efficacy, and risk of depression, logistic regression analyses will be used. Odds ratios, along with their corresponding two-sided 95% confidence intervals, will be obtained for all variables included in these models.

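### The normality rule in section 2.7 covers the primary outcome and lets the data switch body weight from the dyad-aware mixed model to a transformed scale or a rank-sum test

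*Protocol article*

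**What the plan says.** Section 2.7 (Data Analyses) specifies an intention-to-treat comparison of weight loss by a mixed linear model "which accounts for the covariance between the dyad members". The model is fitted to two time points with an arm-by-time interaction, and covariates of interest are included.

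Later in the same paragraph, after the baseline two-group tests and the correlation analyses, the article says that the distributions of continuous study variables will be examined with three kinds of plot and the Kolmogorov-Smirnov (KS) test, and that "any of these variables that deviate from a normal distribution will be transformed prior to analysis or will be analyzed using non-parametric methods". The rank-sum test is the example given. The rule states no exemption for weight, no cut-off, no time point, no level of pooling and no order of preference between the two remedies. Residuals are not mentioned.

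Three other places bear on the point:
- Section 2.6 makes the arm difference in weight loss the one formal test and calls everything else exploratory.
- Section 2.3 randomises dyads, not individuals.
- Section 2.2 sets a lower bound on BMI ("Inclusion criteria were as follows: (1) BMI > 25"), which applies to partners as well as survivors.

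**The concern.** The rule checks the wrong quantity. A mixed model needs residuals that are roughly normal. It does not need the outcome to be normal across a sample that mixes sexes, roles and arms and was selected on BMI.

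Both remedies also alter the primary analysis. A transformation keeps the dyad structure but changes what is estimated: the result is no longer a difference in kg lost, the scale on which section 2.6 plans the trial. A two-group rank-sum test has no term for the dyad covariance, the arm-by-time interaction or the covariates that the same paragraph calls for, and it gives no model-based estimate of kg lost. The choice between keeping the model, transforming and ranking would be made after seeing the data, on the only outcome that is formally tested.

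**Working it through.** **1. The plan's own figure.** Inputs from section 2.6: "two-sided tests at an alpha level of 0.05 will be used"; "a standard deviation of 4.6 kg (from Healthy Moves [39"; "a sample size of 25 dyads per arm (allowing for 90% retention of the initial 28 dyads per arm"; and "there is at least 80% power to detect differences in weight loss of −3.72 kg or greater between the two arms".
- Retention: 28 × 0.9 = 25.2, taken as 25 dyads per arm.
- Standard error of the difference: 4.6 × √(2/25) = 1.301 kg.
- Noncentrality: 3.72 / 1.301 = 2.859.
- Power of the two-sided t-test on 48 degrees of freedom: 0.800 (normal approximation 0.816).

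The stated power reproduces, and nothing below changes it.

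**2. Can BMI be normal?** Table 3 gives mean (SD) 31.8 (5.8) for survivors and 32.9 (6.1) for partners. Normal distributions with these values would place below 25:
- survivors: Φ((25 − 31.8)/5.8) = Φ(−1.172) = 12.1%;
- partners: Φ((25 − 32.9)/6.1) = Φ(−1.295) = 9.8%.

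Eligibility excludes that region, so BMI is not normal. Right skew in weight is then plausible, but it is not shown: the article reports no distribution of weight or height.

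**3. How often would KS at 0.05 reject?** Weight was simulated as BMI × height², with 2,500 to 4,000 runs per scenario.
- From the article: BMI bounded at 25, Table 3 means and SDs, and 8 male survivors and 18 male partners out of 56 each.
- Assumed: four BMI shapes (truncated normal, truncated lognormal, shifted gamma, shifted lognormal); mean heights of 1.60-1.63 m for women and 1.75-1.77 m for men; height SD 0.06-0.09 m. Not every check was run under every combination.

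| Variable tested | Share of trials rejecting normality |
|---|---|
| Raw baseline weight, 112 people, Lilliefors form | 80-95% |
| Raw 6-month weight, 112 people, Lilliefors form | 71-85% |
| Raw baseline weight by role or in one arm, 56 people | 42-74% |
| Raw baseline weight, 112 people, KS not corrected for estimated mean and SD | 23-50% |
| Log baseline weight, 112 people, Lilliefors form | 30-56% |
| Weight change, assumed normal with SD 4.6 kg | about 5% |

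The answer turns almost entirely on which variable is tested and in which form, and the article fixes neither. The plots add a judgement by eye with no stated criterion.

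**4. What would the named fallback do to type I error?** Take a rank-sum test on individual weight changes with both dyad members in the same arm and the pairing ignored. With within-dyad correlation ρ, the variance of the arm contrast is inflated by about 1 + ρ. The actual two-sided error is then about 2 × [1 − Φ(1.96/√(1 + ρ))]:
- ρ = 0: 5.0%;
- ρ = 0.2: 1.96/1.095 = 1.789, giving 7.4%;
- ρ = 0.4: 1.96/1.183 = 1.657, giving 9.8%;
- ρ = 0.6: 1.96/1.265 = 1.550, giving 12.1%.

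Simulation of the rank-sum test itself (25 dyads per arm, normal changes, 4,000 runs) gave 5.1%, 8.3%, 10.4% and 11.7%, in agreement with the approximation. The article gives no value for ρ, so the range is an assumption.

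**The case against.** The best defence is that the sentence is a general one about simple tests. The mixed model is specified first and separately, whereas the normality rule follows the baseline t-tests, the chi-square or Fisher choice and the Pearson or Spearman choice. The rank-sum test is the natural counterpart of a two-group t-test. This reading is possible, but the rule is worded for continuous study variables without limit, and weight is one of them.

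Second, transformation is listed first and keeps the mixed model with its dyad covariance, and the rank-sum test is only an example, so a dyad-level rank test is not excluded. This stands: the loss of dyad structure belongs to one branch of the rule. The other branch still leaves the kg scale.

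Third, a condensed article may leave residual diagnostics to a fuller plan. That is fair, and their absence is not the complaint. The complaint is a rule that the article does state.

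There are stronger readings that the article does not support:
- A reader might infer that the rule will very probably be triggered for weight. That holds only for pooled raw weight in the Lilliefors form, under assumed heights and BMI shapes. Section 2.6 frames the outcome as loss of weight, for which the figure is about 5% if changes are normal.
- A reader might infer that weight must be right-skewed. The entry criterion bounds BMI, not weight.
- A reader might cite the low power (0.15-0.23 for 3.46 kg, with an assumed between-person SD of 17 kg) of a rank-sum test on 6-month weights. The article describes cross-sectional comparisons at baseline only, so that models an analysis it does not state.
- A reader might give the biomarkers equal weight. Their analyses are declared exploratory, and transforming them is already allowed.

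**Conclusion.** The point holds as a defect of wording in an explicit rule. Read literally, section 2.7 allows a check on the data to replace the primary dyad-aware analysis in kg, either by an analysis on another scale or by a rank test that disregards the unit of randomisation. The case does not depend on how likely the rule is to be triggered, which cannot be determined from the article: the simulated range runs from about 5% to about 95%, depending on the variable tested.

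If the rank-sum test were applied to individual changes, type I error would be about 5% with no within-dyad correlation and 12% at a correlation of 0.6. This assumes normal changes, 25 dyads per arm and no allowance for the pairing. The correlation is unknown, but the article itself treats it as something the model must handle.

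**What to change.** Add to section 2.7, or to the analysis plan before the 6-month data are analysed:
- The normality rule does not apply to the primary outcome. Body weight is analysed in kg with the prespecified mixed model, including the dyad covariance, whatever its marginal distribution, and model residuals are inspected.
- Any transformed, robust or rank-based analysis of weight is a sensitivity analysis that respects the dyad, for example dyad-clustered standard errors or a permutation test that reassigns whole dyads.
- Skewed secondary variables are transformed within the same dyad-aware model, not analysed with a rank-sum test on individuals.

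The cost is one or two sentences of analysis text. Sample size, data collection and the stated power calculation do not change. Section 3 reports that the trial was still in the field with statistical analysis to follow, so the change could be made prospectively.

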For our initial statistical analyses that focus on determining potential demographic and cancer-type differences between enrolled DUET cancer survivors and partners, between cancer survivors who express interest in the DUET intervention versus those who refuse or are unresponsive, and those who enroll in the RCT versus those not enrolled, two-group t-tests are performed for continuous variables such as age, and chi-square tests are performed for categorical variables, such as gender, race/ethnicity, residence in a rural- or urban-classified county, and cancer-type. These analyses are now complete, and the results are presented in the next section—findings that are integral in assessing program interest and to appropriately generalize the main outcomes of this trial upon its completion.

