By and large, these are long-term cancer survivors more than five years (M = 67.5 months) out from diagnoses. Given the high representation of breast cancer (80%), it is unsurprising that most participants are female (86%). The age range is broad (i.e., 23–81 years) with a mean age of 58.4 years, and while most participants are employed (55%), one-third are retired. In addition, most (85%) acknowledged at least some college education, with a substantial proportion (43%) reporting annual incomes of at least $50,000 or refusing to answer this question. Minorities comprise almost 40% of the sample, with non-Hispanic Blacks (NHB) having the highest representation; however, very few participants are rural. While most dyads resided separately, over 40% cohabitated with their supportive partners (all of cohabitating partners were in spousal relationships). Both survivors and their supportive partners had average BMI’s falling in the range of Class I obesity (M BMI = 32).

Tests that compared the enrolled DUET cancer survivors (*n* = 56) to partners (*n* = 56) found significant differences for cancer diagnosis (*p* < 0.001), where the proportion of survivors with cancer (100%) was greater than the proportion of partners with cancer (13%), and for gender (*p* = 0.025), where the proportion of female survivors (86%) was greater than the proportion of female partners (68%).

Tests that compared the sample who responded with interest (*n* = 236) and ultimately enrolled in DUET (*n* = 56) to the larger pool who were unresponsive (*n* = 1029) and unenrolled (*n* = 1209) found no significant differences by rural (versus urban) residence or race/ethnicity (*p* > 0.10 for both); however, there were significantly higher response rates among survivors of breast cancer (and hence, females), as well as those who are younger (*p* < 0.05 for both). Though after screening, the only clear difference between enrolled participants versus the potential pool was the proportion of breast cancer survivors, which was significantly higher among enrollees (*p* < 0.0001).

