
**Table 3 nutrients-13-03472-t003:** Study sample characteristics of DUET cancer survivors and partners *.

	Survivors (*n* = 56)	Partners (*n* = 56)	*p*-Value **
Cancer Diagnosis			<0.001
(*n*/%) *			
- Breast	45 (80%)	4 (7%)	
- Colorectal	1 (2%)	0	
- Gynecologic	2 (4%)	2 (4%)	
- Genitourinary	8 (14%)	1 (2%)	
Months elapsed since diagnosis			
- Mean (sd) (*n* = 53)	67.5 (72)		
- Range	10–303		
- Miles between Survivor and Partner (*n*/%)			
- 0 (cohabitate)	24 (43%)		
- Greater than 0, but less than 5	12 (21%)		
- 5 to 10	8 (14%)		
- More than 10	12 (21%)		
Race/Ethnicity			0.8
- Non-Hispanic White	35 (63%)	34 (61%)	
- Hispanic White	0	1 (2%)	
- Non-Hispanic Black	19 (34%)	21 (38%)	
- Hispanic Black	1 (2%)	0	
- Other	1 (2%)	0	
Gender (n/%)			0.03
- Male	8 (14%)	18 (32%)	
- Female	48 (86%)	38 (68%)	
Age (years)			0.1
- Mean (sd)	60.3 (11)	56.5 (14.3)	
- Range	32 79	23 81	
Educational Status			0.9
- High School Graduate	7 (13%)	9 (16%)	
- Some College/Junior College/Trade School	18 (32%)	17 (30%)	
- College Graduate/Post Graduate	30 (54%)	29 (52%)	
- Unknown	1 (2%)	1 (2%)	
Income			0.5
- Less than $50k/year	11 (20%)	7 (13%)	
- $50k/year or more	24 (43%)	23 (41%)	
- Unreported or Refused/Unknown	21 (38%)	26 (46%)	
Rural (*n*/%)	4 (7%)	5 (9%)	1
BMI (kg/m^2^) Mean (sd)	31.8 (5.8)	32.9 (6.1)	0.3
Employment (*n*/%)			1
- Employed	31 (55%)	31 (55%)	
- Retired	18 (32%)	18 (32%)	
- Other	7 (13%)	7 (13%)	

* Information on cancer-type was verified for cancer survivors, but was self-reported for supportive partners. ** For cancer diagnosis, participants with cancer were compared to participants without cancer; for race/ethnicity, only Non-Hispanic Whites and Non-Hispanic Blacks were compared; for educational status, participants with a response of unknown were excluded from the analysis.

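### Survivor-versus-partner comparisons use independent-sample tests on 56 matched pairs, and the reported gender difference is borderline once the pairing is respected (minor)

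*Protocol article*

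**What the plan says.** Section 2.7 (Data Analyses) sets out initial analyses of three comparisons. The first concerns "potential demographic and cancer-type differences between enrolled DUET cancer survivors and partners". The other two compare interested survivors with those who refused or did not respond, and enrolled survivors with those not enrolled. For all three, "two-group t-tests are performed for continuous variables such as age, and chi-square tests are performed for categorical variables, such as gender". The section adds that these analyses are complete and that they matter for judging interest and for generalising the trial's results.

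The pairing comes from the design. Under section 2.2, "the survivor was asked to identify a local support partner (preferably within a 10-min drive"), and section 2.6 describes the sample as "56 dyads (with each dyad comprised of a survivor and a partner").

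Section 3 reports two significant survivor-partner differences: cancer diagnosis (p < 0.001) and gender (86% v 68% female, p = 0.025). Table 3 gives the remaining p-values. The significance rule in section 2.7 is: "Statistical tests will use an alpha level of 0.05 and will be two-sided".

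**The concern.** A two-group t-test or chi-square test takes the two samples as independent. Here each person in one column of Table 3 is tied to one person in the other. The variance of the difference then includes a within-dyad covariance term, which the unpaired tests set to zero. Positive association within dyads makes the unpaired p-value too large. Negative association, as with gender in opposite-sex couples, makes it too small.

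The article recognises this dependence for the primary outcome, which is analysed "using a mixed linear model which accounts for the covariance between the dyad members", but does not carry it into the survivor-partner comparison described later in the same section.

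What is at stake is how the sample is described. Gender is the only informative significant survivor-partner difference reported. The cancer-diagnosis test tells the reader nothing, because survivors have cancer by definition.

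**Working it through.** **Inputs (Table 3, n = 56 per column).** Male: 8 survivors, 18 partners. Age, mean (SD): 60.3 (11) v 56.5 (14.3). BMI: 31.8 (5.8) v 32.9 (6.1). Cohabiting dyads: 24, all spousal according to section 3. Not reported: the within-dyad gender table and any within-dyad correlation.

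**Reproducing the article's figures.**
- Gender, Pearson chi-square without continuity correction: 112 × (8×38 − 48×18)² / (26 × 86 × 56 × 56) = 5.009, p = 0.0252. The article gives 0.025.
- Age, two-group t: 3.8 / √((11² + 14.3²)/56) = 1.576, p = 0.118. Table 3 gives 0.1.
- BMI, two-group t: −1.1 / √((5.8² + 6.1²)/56) = −0.978, p = 0.330. Table 3 gives 0.3.

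So the unpaired tests were used as described.

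**Gender, paired.** Let d be the number of dyads in which both members are male. The margins give b = 18 − d dyads with a female survivor and male partner, and c = 8 − d with a male survivor and female partner, for d = 0 to 8. Uncorrected McNemar is (b − c)²/(b + c) = 100/(26 − 2d). The exact test is a two-sided binomial test of b out of b + c at 0.5.

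| d | b v c | Uncorrected p | Continuity-corrected p | Mid-p | Exact p |
|---|---|---|---|---|---|
| 0 | 18 v 8 | 0.0499 | 0.078 | 0.052 | 0.076 |
| 1 | 17 v 7 | 0.041 | 0.066 | 0.043 | 0.064 |
| 2 | 16 v 6 | 0.033 | 0.055 | 0.035 | 0.053 |
| 3 | 15 v 5 | 0.025 | 0.044 | 0.027 | 0.041 |
| 8 | 10 v 0 | 0.0016 | 0.0044 | 0.001 | 0.002 |

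With no association within dyads, the expected d is 8 × 18/56 = 2.6. Below that, the unpaired p-value is too small; above it, too large.

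If all 24 spousal dyads are opposite-sex (an assumption; the article does not say), each is discordant. Then 26 − 2d ≥ 24, so d ≤ 1 and the first two rows apply.

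**Age, paired.** t = 3.8 / √((11² + 14.3² − 2r × 11 × 14.3)/56) on 55 degrees of freedom, with r assumed:

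| r | t | p |
|---|---|---|
| −0.2 | 1.443 | 0.155 |
| 0 | 1.576 | 0.121 |
| 0.3 | 1.871 | 0.067 |
| 0.5 | 2.193 | 0.033 |

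p falls below 0.05 only when r exceeds about 0.39.

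**BMI, paired.** The same formula gives p = 0.332 at r = 0 and 0.173 at r = 0.5. It falls below 0.05 only when r exceeds about 0.76.

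**Items whose conclusion cannot change.**
- Cancer diagnosis: 4 + 2 + 1 = 7 partners report cancer, so 49 v 0 dyads are discordant and p < 0.001.
- Employment: the margins are identical (31, 18, 7 in both columns), so a paired test of the margins gives p = 1.
- Rural (4 v 5): the net difference is one dyad. The smallest possible uncorrected McNemar p is 0.317, from one discordant dyad.
- Race (19 v 21 Non-Hispanic Black): for a net difference of two dyads, the smallest uncorrected p is 0.157, from two discordant dyads. Dropping dyads with a member outside the two compared groups could raise the net difference to three at most, for a statistic of at most 9/3 = 3, still below the 3.84 needed.

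Education and income also depend on unreported cross-tables; I have not bounded them.

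**The case against.** The strongest reply is that pairing alone does not overturn the gender result. The like-for-like replacement for an uncorrected chi-square is the uncorrected McNemar test, which stays at or below 0.0499 in every table the margins allow. Reaching 0.064 to 0.076 takes a second change, from an asymptotic to an exact test, and Fisher's exact test on the unpaired data already moves 0.025 to 0.043. This stands. A reader might infer that the gender difference disappears, but the article's data do not show that. The observed 86% v 68% is the same under any test.

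A reader might also infer that every p-value in Table 3 misleads, or that the direction of each error is known. Neither is supported. Four conclusions cannot change, and the direction for gender, age and BMI rests on within-dyad data that are not reported. Partners include friends and neighbours as well as spouses and other family (Discussion), so a high age correlation cannot be taken for granted. Nor does section 3 draw any survivor-partner age conclusion; its age finding concerns which survivors responded.

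Finally, section 2.6 labels everything except the weight comparison exploratory, and the Discussion and Conclusions do not lean on the survivor-partner gender test. That stands too, and it limits the severity. It does not excuse the test: the analysis is stated, complete and reported, so it is not a detail left to another document.

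**Conclusion.** The point holds as a minor one. The survivor-partner p-values in section 3 and Table 3 rest on the wrong error structure. The practical consequence is that p = 0.025 for gender conveys more certainty than the data may carry. If the spousal dyads are opposite-sex, the result is borderline and its side of 0.05 depends on the version of McNemar's test. Without that assumption, exact p lies anywhere from 0.002 to 0.076, and it exceeds 0.05 only when at most two dyads are male-male. Age could cross 0.05 in the other direction, but only with a within-dyad correlation above about 0.39.

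The interested-versus-unresponsive and enrolled-versus-not-enrolled comparisons are not survivor-partner pairs, so this point does not touch them. The randomised weight analysis already models dyad covariance and is unaffected.

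**What to change.** For the survivor-partner comparisons only:

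- Use paired t-tests for continuous variables, McNemar's test for binary variables, and Stuart-Maxwell or Bowker for variables with more than two categories. Stuart-Maxwell compares the margins, which is what Table 3 displays. Paired differences with 95% confidence intervals would serve equally well.
- Name the version of McNemar's test (exact, mid-p or uncorrected), since the gender result may turn on it.
- Report the within-dyad gender cross-table.
- Drop the cancer-diagnosis p-value and keep the counts.
- Update the Table 3 p-values and the gender statement in section 3, and limit the two-group tests in section 2.7 to the other two comparisons.

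The cost is rerunning one descriptive table on data already collected.
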